#### 5. Analysis of secondary endpoints

- a. Adverse events are evaluated by the CTEP Active Version of the NCI Common Terminology Criteria for Adverse Events (CTCAE). The treatment-related attribution includes definitely, probably or possibly related to treatment. An acute adverse event is defined as the first occurrence of worst severity of the adverse event  $\leq 30$  days after the completion of RT. A late adverse event is defined as the first occurrence of worst severity of adverse event  $> 30$  days after RT completion.
- b. Biochemical failure-free survival
  - Biochemical failure-free survival will be measured from the date of registration to the date of documentation of biochemical recurrence (RTOG phoenix definition) or until the date of death from any cause. DFS at 1, 2, and 5 years will be estimated by the Kaplan-Meier method. Also, 95% confidence intervals will be reported.

- c. Disease-specific survival
  - The disease-specific survival duration will be measured from the date of registration to the date of documentation of death due to prostate cancer or until the date of death from any cause. DSS at 1, 2, and 5 years will be estimated by the Kaplan-Meier method. Also, 95% confidence intervals will be reported.
- d. Overall survival
  - The overall survival duration will be measured from the date of registration to the date of documentation of death from any cause. OS at 1, 2, and 5 years will be estimated by the Kaplan-Meier method. Also, 95% confidence intervals will be reported.

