### **Secondary Objectives**

- To estimate the rate of acute and late GI and GU toxicity for each arm at 1, 2, and 5 years
- To estimate biochemical-failure free survival in each arm at 1, 2, and 5 years
- To estimate disease-specific survival in each arm at 1, 2, and 5 years
- To estimate overall survival in each arm at 1, 2, and 5 years

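### As worded, disease-specific survival ends at death from any cause with no censoring rule, so read literally it duplicates overall survival

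*Protocol*

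**What the plan says.** Section 8.0, item 5 of the protocol defines three time-to-event endpoints that bear on this point.

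- **Item 5.b, biochemical failure-free survival**, runs from registration to "biochemical recurrence (RTOG phoenix definition) or until the date of death from any cause".
- **Item 5.c, DSS:** "The disease-specific survival duration will be measured from the date of registration" and it runs "to the date of documentation of death due to prostate cancer or until the date of death from any cause". The estimator is given as "DSS at 1, 2, and 5 years will be estimated by the Kaplan-Meier method", with 95% confidence intervals.
- **Item 5.d, OS:** "The overall survival duration will be measured from the date of registration to the date of documentation of death from any cause". The estimator is given as "OS at 1, 2, and 5 years will be estimated by the Kaplan-Meier method", again with 95% confidence intervals.

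The Secondary Objectives, in the Protocol Summary and again in section 2.0, list the two as separate aims: "To estimate disease-specific survival in each arm at 1, 2, and 5 years" and "To estimate overall survival in each arm at 1, 2, and 5 years". Section 8.0, item 2 also lists them as separate secondary endpoints. No part of the protocol says how a death from another cause is to be handled for DSS.

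**The concern.** DSS is useful beside OS only if it separates deaths from the disease from other deaths. The definition in 5.c names prostate-cancer death and then adds death from any cause as an alternative end of the interval. With no censoring rule, an analyst who follows the text would count an unrelated death as a DSS failure. The protocol would then report OS twice under two names, and the DSS objective would go unanswered.

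The result could also be used. Section 8.0, item 4 allows secondary results to inform which regimen is preferred if both arms are acceptable on quality of life. An unrelated death would then count against an arm in both DSS and OS.

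This is not a detail left to a statistical analysis plan. The protocol states a definition. A plan that followed it would repeat the problem, and one that departed from it would contradict the protocol.

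**Working it through.** The protocol states no DSS or OS figure, so there is none to reproduce. The check is first logical, then illustrative.

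**1. The two definitions side by side**

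| | DSS (5.c) | OS (5.d) |
|---|---|---|
| Origin | registration | registration |
| End | prostate-cancer death, or any death | any death |
| Estimator | Kaplan-Meier | Kaplan-Meier |
| Times | 1, 2, 5 years | 1, 2, 5 years |
| Censoring of other-cause death | not stated | not applicable |

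Prostate-cancer deaths are a subset of all deaths. For every patient, therefore, min(T_prostate-cancer death, T_any death) = T_any death. If each listed death is an event, the DSS and OS times and event indicators coincide, and so do the Kaplan-Meier curves.

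**2. Numerical confirmation**

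Death times were simulated with constant cause-specific hazards for 200,000 patients per scenario. The 5-year net risks are assumptions and are not in the protocol.

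| Assumed risk, prostate / other | OS | DSS as written | DSS, other deaths censored (theory) |
|---|---|---|---|
| 1% / 5% | 93.99% | 93.99% | 99.0% |
| 2% / 10% | 88.22% | 88.22% | 98.0% |
| 2% / 15% | 83.35% | 83.35% | 98.0% |

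The individual DSS and OS times were identical in all three scenarios. In samples of 64 the Kaplan-Meier estimates also agreed. In the first scenario both were 0.906, against 0.984 with other-cause deaths censored.

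**3. Size with no prostate-cancer deaths**

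True DSS is then 100%, and DSS as written is (1 − m)^t, where m is the assumed yearly other-cause mortality.

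| m | 1 year | 2 years | 5 years | Error at 5 years |
|---|---|---|---|---|
| 0.5% | 99.5% | 99.0% | 0.995^5 = 97.5% | 2.5 points |
| 1% | 99.0% | 98.0% | 0.99^5 = 95.1% | 4.9 points |
| 2% | 98.0% | 96.0% | 0.98^5 = 90.4% | 9.6 points |
| 3% | 97.0% | 94.1% | 0.97^5 = 85.9% | 14.1 points |

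**4. Effect of a single death**

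Section 8.0, item 3 sets 32 patients per arm. One non-cancer death, with no earlier censoring, lowers the arm's DSS as written by 1/32 = 3.1 points.

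**5. Does the choice of remedy matter?**

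Compare one minus Kaplan-Meier, with other deaths censored, to the cumulative incidence of prostate-cancer death. Under constant hazards the cumulative incidence is [λp / (λp + λo)] × (1 − OS).

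- For 2% / 10%: λp = −ln(0.98)/5 = 0.00404 and λo = −ln(0.90)/5 = 0.02107. Cumulative incidence = (0.00404/0.02511) × 11.8% = 1.90%, against 2.0%.
- For 2% / 15%: λo = −ln(0.85)/5 = 0.03250. Cumulative incidence = (0.00404/0.03654) × 16.7% = 1.85%, against 2.0%.

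The difference is 0.10 to 0.15 points, small beside the 3.1 points that one death moves an arm.

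**The case against.** The strongest defence is that 5.c describes how a duration is measured and never calls death from any cause an event. If every death were an event, naming prostate-cancer death would be redundant. Because DSS and OS are listed separately, the authors presumably meant follow-up to stop, censored, at another death. That is a fair account of the likely intent. It does not rescue the wording: 5.c mentions no censoring, and the same clause in 5.b closes a failure-free time in which death naturally counts as a failure. Nothing tells the analyst to read the same words in opposite ways in adjacent items. One might suppose that the clause was carried over from 5.b, but that is inference.

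Three stronger readings are tempting, and the documents do not support them.

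- *The error is 10 to 14 points.* That needs 2% to 3% yearly other-cause mortality and applies only at 5 years. The protocol gives no mortality rate or age distribution. Section 3.0 sets no upper age limit, but it requires ECOG 0-1 and excludes most previous cancers and several serious cardiac and respiratory conditions. Lower rates are therefore as plausible as higher ones.
- *Kaplan-Meier must be replaced by a competing-risks estimator.* With rare prostate-cancer deaths the two differ by about 0.1 to 0.15 points in the scenarios above. Kaplan-Meier with other deaths censored is a recognised cause-specific estimate.
- *The trial's main conclusion is at risk.* The sample size and decision rule rest on 1-year EPIC change. DSS is only to be estimated, with no test or threshold. Item 4 permits secondary results to be considered but does not give DSS a fixed role.

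**Conclusion.** The point holds as a defect in a stated definition. Taken literally, and consistently with 5.b, item 5.c makes DSS the same quantity as OS and defeats the separate DSS objective. At best the wording leaves two different quantities open.

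The size depends on an assumed mortality rate. With no prostate-cancer deaths and 0.5% to 3% yearly other-cause mortality, the understatement of DSS is about 0.5 to 3 points at 1 year and 2.5 to 14 points at 5 years. Severity is moderate: the correction is worth making before analysis because secondary results may inform the choice of regimen, but the primary endpoint, its test, the sample size and the definition of OS all stand.

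**What to change.** Amend section 8.0, item 5.c in two respects.

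1. State that only death due to prostate cancer is a DSS event.
2. State how other deaths are handled. Either censor them at the date of death and report cause-specific Kaplan-Meier estimates, or treat them as a competing event and report the cumulative incidence of prostate-cancer death. Give 95% confidence intervals at 1, 2 and 5 years per arm in either case. Both options cure the defect. Cumulative incidence is the more direct statement of absolute risk, but the choice will matter little if prostate-cancer deaths are rare.

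Confirm that cause of death is recorded. The schedule in Appendix I has no line for it, and on the literal reading of 5.c it would not be needed. Leave item 5.d unchanged.

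The cost is a sentence or two in the protocol and, if it is not already there, one field on the follow-up form. Design, sample size and visit schedule do not change.

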## **9.0 Data and protocol management**

The data management will be conducted in compliance with the protocol, the International Conference on Harmonisation of Good Clinical Practice (ICH GCP) guidelines and the Declaration of Helsinki. The protocol will be adhered and complied to the principle of ICH-GCP.

All collected data will be saved in electronic database securely and confidentially with password protected. Private information (i.e. name, address, identity number etc) will not be included in database and collected information will only be identified by an anonymous code for each patient. Authority to access private information will only be provided to the respective investigators and their designee. It is the responsibility of each investigator to manage the collected data securely and to protect private information.

## **10.0 Publication Policy**

The study results shall be presented at international academic conferences and the final report shall be submitted for publication in peer reviewed international journal. This will be determined by the principle investigator. Prior to any submission for presentation or publication, an approval should be obtained from the principal investigators. Supporting groups should be acknowledged.

## Appendix I

|                                                                  | Pre-study entry |         |          |          | During treatment | Follow-up (months)
Every 6 months for years 3, 4, and 5, then annually |   |   |    |    |    |    |    |
|------------------------------------------------------------------|-----------------|---------|----------|----------|------------------|---------------------------------------------------------------------------|---|---|----|----|----|----|----|
|                                                                  | ≤60days         | ≤90days | ≤180days | ≤365days | Weekly during RT | 3                                                                         | 6 | 9 | 12 | 15 | 18 | 21 | 24 |
| History/physical exam including digital rectal examination (DRE) | X               |         |          |          |                  |                                                                           |   |   |    |    |    |    |    |
| Physical exam including DRE                                      |                 |         |          |          |                  | X                                                                         | X | X | X  | X  | X  | X  | X  |
| Performance status                                               | X               |         |          |          | X                | X                                                                         | X | X | X  | X  | X  | X  | X  |
| Prostate biopsy with Gleason score                               |                 |         |          | X        |                  |                                                                           |   |   |    |    |    |    |    |
| PSA                                                              | X               |         |          |          |                  | X                                                                         | X | X | X  | X  | X  | X  | X  |
| Testosterone                                                     |                 |         | X        |          |                  |                                                                           |   |   |    |    |    |    |    |
| Adverse event evaluation                                         |                 |         |          |          | X                | X                                                                         | X | X | X  | X  | X  | X  | X  |
| MRI pelvis                                                       | X               |         |          |          |                  |                                                                           |   |   |    |    |    |    | X* |
| Bone scan                                                        | X*              |         |          |          |                  |                                                                           |   |   |    |    |    |    | X* |
| EPIC questionnaire                                               | X               |         |          |          |                  | X                                                                         | X | X | X  |    | X  |    | X  |
| * if clinically indicated                                        |                 |         |          |          |                  |                                                                           |   |   |    |    |    |    |    |

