#### **4.0 Pre-treatment evaluation and management**

Patients recruited into this study are required to complete the investigation including MRI pelvis. Bone scan will be required if clinically suspicious of bone metastasis. Besides, three gold fiducial markers will be inserted into the prostate under trans-rectal ultrasound (TRUS). The markers will be inserted in different planes within the prostate in order to facilitate the visualization of these markers in the on-board imaging at antero-posterior and lateral position.

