### 3. Radiation therapy adverse events

- All patients will be seen weekly by their radiation oncologist during radiation therapy. Any observations regarding radiation reactions will be recorded and should include attention to the following potential side effects:
  - Small bowel or rectal irritation manifesting as abdominal cramping, diarrhea, rectal urgency, proctitis, or hematochezia; □
  - Bladder complications including urinary frequency/urgency, dysuria, hematuria, urinary tract infection, and incontinence;
  - Radiation dermatitis.
- Clinical discretion may be exercised to treat side effects from radiation therapy. Diarrhea/rectal frequency/urgency may be managed with diphenoxylate or loperamide. Bladder irritation may be mitigated with phenazopyridine. Urinary frequency/urgency can be managed with anticholinergic agents or alpha-blockers such as tamsulosin. Erectile dysfunction can be managed with phosphodiesterase (PDE) inhibitors such as sildenafil.
- Adverse Events (AEs) and Serious Adverse Events (SAEs) Reporting Requirements
  - **Definition of an AE:** Any unfavorable and unintended sign (including an abnormal laboratory finding), symptom, or disease temporally associated with the use of a medical treatment or procedure regardless of whether it is considered related to the medical treatment or procedure (attribution of unrelated, unlikely, possible, probable, or definite). [CTEP, NCI Guidelines: Adverse Event Reporting Requirements. January 2005;
  - **Definition of an SAE:** Any adverse experience occurring during any part of protocol treatment and 30 days after that results in any of the following outcomes:
    - ◆ Death;
    - ◆ A life-threatening adverse experience;
    - ◆ Inpatient hospitalization or prolongation of existing hospitalization;
    - ◆ A persistent or significant disability/incapacity;
    - ◆ A congenital anomaly/birth defect.
- Important medical events that do not result in death, are not life threatening, or do not require hospitalization may be considered an SAE, when, based upon medical judgment, they may jeopardize the patient and may require medical or surgical intervention to prevent one of the outcomes listed in the definition. Any pregnancy occurring on study must be reported via CCTU as a medically significant event.

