### 6.0 Hormonal therapy

Neoadjuvant androgen deprivation (ADT) will be given to intermediate risk patients (T2b-c or GS 7 or PSA 10-20) before the start of radiotherapy. Two injections of ADT (every 3 months) will be given prior radiotherapy and the radiotherapy will be started 1 month after the last injection of ADT.

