From the conventional arm of RTOG 0415, in an analysis of 108 patients (mean pretreatment score 94 with SE=9 and range 61-100), 38 patients (35%) had a change in EPIC bowel domain score (baseline to 1-year) that was worse than 5 points. For 110 patients (mean pretreatment score 88, SE=12, range 35-100), 43 (39%) had a change in EPIC urinary domain score that was worse than 2 points. Mean reduction in bowel and urinary scores have also been published in a historical series by Wei et al. (2002). The mean reduction in bowel and urinary scores observed in the RTOG 0415 analysis are in keeping with the series published by Wei. Standard radiotherapy in regimens such as used in the conventional arm of 0415 is well tolerated. Thus the HRQOL analysis from the 0415 study will be used in the sample size calculation. The percentage of patients with change in EPIC bowel domain score (baseline to 1-year) that was worse than 5 points and a change in EPIC urinary domain score that was worse than 2 points are felt to be clinically meaningful endpoints to assess for tolerability and safety.

A rate for the worse-than-5 point change in bowel score of up to 35% of patients will be considered acceptable, with a rate  $\geq 60\%$  specified as unacceptable. Similarly, a rate for the worse-than-2 point change in urinary score of up to 40% will be considered acceptable, with a rate  $\geq 65\%$  unacceptable. Using the normal approximation to the binomial distribution for  $p$ , the formula to calculate the sample size is given by:

$$n = \left[ \frac{z_{1-\alpha} \sqrt{p_0(1-p_0)} + z_{1-\alpha} \sqrt{p_a(1-p_a)}}{(p_0 - p_a)} \right]^2$$

where  $p_0$  is as previously defined,  $p_a$  = the alternative probability,  $z_q$  = 100(qth) percentile of the standard normal distribution. With the aforementioned design parameters, a sample size of 60 eligible patients (30 per arm) is required with 80% power and significance level 0.025 (one-sided test). The significance level 0.025 will be used for each endpoint in order to preserve an overall significance level of 0.05. Adjusting for 5% ineligibility, **the required sample size is 64 patients (32 per arm).**

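### No adverse event grade is scheduled before radiotherapy, so pre-existing GI/GU symptoms can enter the acute toxicity rates

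*Protocol*

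**What the plan says.** The Appendix I row "Adverse event evaluation" has no mark in any of the four pre-study columns. Its marks start in the weekly on-treatment column and continue at months 3, 6, 9, 12, 15, 18, 21 and 24. Performance status, PSA and EPIC all have a pre-study mark. No column covers the interval between study entry and RT.

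The text agrees with the table. Section 5.0, item 3, says "All patients will be seen weekly by their radiation oncologist during radiation therapy" and places the recording of reactions at those visits. Section 7.0, part B, also documents acute reactions during RT.

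Two protocol procedures fall before the first fraction. Section 4.0 has three gold markers placed in the prostate under trans-rectal ultrasound in every recruited patient. Section 6.0 says "Neoadjuvant androgen deprivation (ADT) will be given to intermediate risk patients", that "Two injections of ADT (every 3 months) will be given prior radiotherapy", and that "the radiotherapy will be started 1 month after the last injection of ADT". Section 3.0 excludes men with previous hormonal therapy, so this treatment follows entry.

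Section 8.0, item 5a, states: "An acute adverse event is defined as the first occurrence of worst severity of the adverse event", up to 30 days after RT ends. Late events are those first reaching worst severity after that. The acute definition gives neither a start date nor a comparison with baseline. Acute and late GI/GU toxicity rates per arm are the first secondary endpoint in Section 8.0, item 2.

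**The concern.** A toxicity rate attributed to radiotherapy needs a record of what the patient had before it. Without a pre-RT grade, a long-standing urinary symptom and one caused by the first week of treatment leave the same entry in the database. The acute rate in each arm can then include background symptoms, and the investigator has no documented starting grade when judging relatedness.

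Non-serious harm from marker insertion or hormonal therapy is also not looked for at any scheduled evaluation, although both are protocol procedures.

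This is a gap in data collection. A later analysis plan can define a baseline-adjusted rate, but it cannot recover a grade that nobody recorded before the first fraction.

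**Working it through.** **Interval before RT.** For intermediate-risk men, Section 6.0 gives 3 months between the two injections plus 1 month to RT: 3 + 1 = 4 months. Low-risk men receive no hormonal therapy, so for them the interval holds only the marker insertion. The protocol does not say when markers are placed relative to the injections.

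**Tracing two patients through the schedule.**

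| Step | Patient A: stable grade 2 urinary frequency since before entry | Patient B: no symptom until RT week 1, then grade 2 |
|---|---|---|
| Pre-study columns | not graded | not graded |
| After markers / during hormonal therapy | not graded | not graded |
| First weekly RT visit | grade 2 recorded | grade 2 recorded |
| Section 8.0, item 5a | acute event, unless attributed as unrelated or unlikely | acute event |

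Only the relatedness judgement can separate A from B, and it is made without a pre-RT grade.

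**Late events.** Patient A's symptom reaches its worst grade at the first RT visit. If it stays stable, it is not a late event on the plain reading of the definition. The point therefore concerns the acute rates.

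**Denominator.** Section 8.0 gives 30 eligible patients per arm and 5% ineligibility: 30 / (1 - 0.05) = 31.6, rounded up to 32, as stated. The protocol gives no anticipated toxicity rate to reproduce.

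**Range of the effect (assumption).** Let b be the share of men with a grade 2 GU symptom before RT that attribution does not remove. With b from 0 to 20%, the number affected is 0 x 32 = 0 to 0.20 x 32 = 6.4 per arm. If b is independent of a true RT rate r, the observed rate is 1 - (1 - r)(1 - b). For r, take three GU rates (grade 2 or above) from the SBRT table in Section 1.0, as examples only:

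| r | b = 0 | b = 5% | b = 10% | b = 20% |
|---|---|---|---|---|
| 8.5% | 8.5% | 13.1% | 17.6% | 26.8% |
| 20% | 20% | 24.0% | 28.0% | 36.0% |
| 31% | 31% | 34.5% | 37.9% | 44.8% |

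The first column applies if no such symptom exists or if attribution removes every one. Nothing in the protocol says where in this range b lies. The reference cohort in Section 8.0 had a mean pretreatment urinary score of 88 with a range of 35-100, so some men had symptoms. But the minimum may be a single patient, and the protocol has no rule that turns an EPIC score into a CTCAE grade.

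**The case against.** The strongest reply is that the protocol already has filters.

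- **Attribution.** Section 8.0, item 5a, defines which events count as treatment-related, and Section 5.0 provides for events judged unrelated or unlikely. A symptom known to predate treatment could be removed this way. This stands in part. Possible relatedness is enough to count, treatment is not confined to RT, and the text does not say that the reported rates are limited to related events.
- **Baseline records.** A history and physical is required, and baseline EPIC is mandatory. EPIC asks about blood in the urine, night-time and daytime frequency, rectal urgency and rectal bleeding. The investigator does have a starting record. It is not a CTCAE grade, however, and for intermediate-risk men it was taken before about 4 months of hormonal therapy.
- **Serious events.** The SAE definition in Section 5.0 covers all protocol treatment and 30 days beyond, so it may capture serious events before RT. It does not create a scheduled check for the others.
- **Analysis conventions.** Counting only grades above baseline is often left to a statistical analysis plan, and its absence alone would be no defect. The uncollected grade is a matter for the protocol.

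A reader might also infer more than the document supports:

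- That pre-existing symptoms certainly enter the rates. Attribution may remove some or all, so the defensible wording is that they can.
- That late rates are inflated in the same way. A stable symptom would not be late on the plain reading.
- That the choice between regimens is compromised. Section 8.0, item 4, only allows secondary endpoints to be considered, and only when both arms are acceptable on EPIC. The co-primary endpoints use change from each patient's own baseline. Randomization is stratified by risk group, so hormonal therapy should be balanced by design and background symptoms in expectation. With 32 per arm, chance imbalance remains possible.

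**Conclusion.** The point holds in a limited form. Followed as written, the protocol never collects a CTCAE grade before RT, and its acute definition has no start date or baseline reference. Pre-existing or pre-RT GI/GU symptoms can therefore be counted in the acute toxicity rates. The missing evaluation after marker insertion applies to all patients, and the roughly 4-month gap during hormonal therapy to intermediate-risk patients only.

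The main effect is possible inflation of each arm's own acute rate, a secondary endpoint. The primary analysis is untouched. Its size is unknown: 0 to about 6 of 32 per arm if 0-20% of men had a grade 2 GU symptom that attribution did not remove. Both ends of that range are assumptions. The change is worth making because it is cheap and the missing grade cannot be reliably recovered afterwards.

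**What to change.** In Appendix I, mark the adverse event row at pre-study entry, alongside the history and physical already scheduled, and again before the first fraction. The second entry should ask about events since marker insertion and, where given, since the start of hormonal therapy. The planning CT takes place with any markers in place, so it or the first treatment attendance could serve as the contact.

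In Section 8.0, item 5a, start acute events at the first fraction. Report GI/GU toxicity as grades above the pre-RT grade, with crude rates shown alongside if wanted. List events between registration and the first fraction separately.

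The cost is two extra adverse event entries per patient, with no new visit or procedure. Baseline-adjusted rates are less directly comparable with published crude rates, which is the reason for showing both.
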